## Abstract

**Introduction:**

In the field of arthroscopic rotator cuff repair (ARCR), reporting standards of published studies differ dramatically, notably concerning adverse events (AEs). In addition, prognostic studies are overall methodologically poor, based on small data sets and explore only limited numbers of influencing factors. We aim to develop prognostic models for individual ARCR patients, primarily for the patient-reported assessment of shoulder function (Oxford Shoulder Score (OSS)) and the occurrence of shoulder stiffness 6 months after surgery. We also aim to evaluate the use of a consensus core event set (CES) for AEs and validate a severity classification for these events, considering the patient’s perspective.

**Methods and analysis:**

A cohort of 970 primary ARCR patients will be prospectively documented from several Swiss and German orthopaedic clinics up to 24 months postoperatively. Patient clinical examinations at 6 and 12 months will include shoulder range of motion and strength (Constant Score). Tendon repair integrity status will be assessed by ultrasound at 12 months. Patient-reported questionnaires at 6, 12 and 24 months will determine functional scores (subjective shoulder value, OSS), anxiety and depression scores, working status, sports activities, and quality of life (European Quality of Life 5 Dimensions 5 Level questionnaire). AEs will be documented according to a CES. Prognostic models will be developed using an internationally supported regression methodology. Multiple prognostic factors, including patient baseline demographics, psychological, socioeconomic and clinical factors, rotator cuff integrity, concomitant local findings, and (post)operative management factors, will be investigated.

**Ethics and dissemination:**

This project contributes to the development of personalised risk predictions for supporting the surgical decision process in ARCR. The consensus CES may become an international reference for the reporting of complications in clinical studies and registries. Ethical approval was obtained on 1 April 2020 from the lead ethics committee (EKNZ, Basel, Switzerland; ID: 2019-02076). All participants will provide informed written consent before enrolment in the study.

**Trial registration number:**

NCT04321005.

**Protocol version:**

Version 2 (13 December 2019).

Strengths and limitations of this studyThis is a large prospective multicentre observation of routine care.The study is an assessment of patient-reported outcomes.The study will implement an international core outcome set of adverse events.The study will use internationally supported methodology for prognostic model development.There is potential limited response to patient questionnaires at 24 months.

## Introduction

Rotator cuff tears are one of the most common injuries of the shoulder joint, which may cause pain and disability associated with severe restrictions in daily activities. Surgical repair is indicated when non-operative treatment fails or follows extended traumatic tears, notably inactive patients without signs of advanced tendon degeneration or muscle fat infiltration.^1^ Clinical studies have demonstrated clinically relevant improvement in shoulder function and quality of life after arthroscopic rotator cuff repair (ARCR).^2–5^ The number of ARCRs has increased over the last two decades^6–9^ due to several contributing factors, such as an ageing yet active population, improvements in operative repair techniques and more liberal indications for ARCRs.

Not all patients, however, benefit from ARCR.^10^ Patients may be affected by complications and/or adverse events (AEs) such as persistent pain, shoulder stiffness, infection, neurological problems and repair failures.^11 12^ About 20% of patients may show, typically between 6 and 12 months following ARCR, a persistent rotator cuff defect.^13^ Patients with healed tendons may show better functional outcome after repair.^2 14 15^ Postoperative shoulder stiffness, a major complication reported to occur in 1.5%–11.1% of ARCRs,^11^ leads to limitations in everyday activities, prolonged rehabilitation, and in severe cases to reoperation (capsular release).^16–18^ Nonetheless, incident data on outcome and AEs are impaired by the heterogeneity in definition and reporting.^13 19^

Valid and representative data on the safety and effectiveness of ARCR are non-existent at the Swiss national level. However, such data are paramount for optimising the indication and outcome of ARCR and for benchmarking orthopaedic clinics. Reporting standards are a prerequisite for outcome and safety data. Recently, a core outcome set (COS)^20^ was defined for shoulder disorders, which includes inner core domains of pain, physical function and activities, global perceived effect (a person’s assessment of their recovery or degree of improvement), and AEs.^21 22^ A core event set (CES) was developed by international consensus in ARCR^12 23^ and lay the ground for the current project.

Appropriate indication of ARCR and judgement on risks of AEs or unsatisfactory patient outcomes rely on validated clinical prediction tools,^24 25^ which are still sparse in the field of surgical repair of a rotator cuff tear. Currently existing models focus on early surgical repair,^26^ tendon healing^27 28^ or shoulder functional outcomes.^29^ A model for shoulder stiffness included patients with various shoulder pathologies and surgeries.^30^ Furthermore, individual outcome predictions in ARCR require the identification of relevant patient and management factors. Several systematic reviews have highlighted the general lack of qualitative studies focused on prognostic factors for ARCR outcomes.^31–35^ In addition, we have observed substantial heterogeneity in terms of applied methodology, core outcomes and studied prognostic factors, where certain factors (eg, age, tear size, muscle degeneration, smoking) are given greater focus over others (eg, sex, traumatic onset). The reviews highlight the need for more robust prospective studies to include additional patient-reported outcomes in a multivariable context.

### Objectives

The *overall objective* is to establish a prospective cohort of patients undergoing ARCR with standardised data collection and follow-up for the evaluation and prediction of targeted core safety, and clinical and patient-reported outcome parameters that are to be routinely collected in standard clinical care.

The *primary objective* is to develop predictive models for two core outcome parameters: (1) patient-reported Oxford Shoulder Score (OSS) functional outcome; and (2) occurrence of shoulder stiffness (primary safety event) as reported by patients and clinicians.

The *secondary objectives* are (1) to evaluate the content and applicability of the defined consensus CES (ie, ARCR CES 1.0)^23^ in routine practice considering the patient’s perspective; (2) to quantify the incidence of AE up to 24 months after surgery (eg, persisting or worsening pain, recurrent rotator cuff defect); (3) to validate an adapted severity classification for postoperative local AEs^12 36^; and (4) to develop predictive models for other clinically relevant outcome parameters, including patient-reported outcomes (eg, perception of improvement, return to work, return to sports, quality of life, satisfaction with surgery, acceptability of symptom state), clinical outcomes (eg, shoulder strength and motion) and specific AEs (eg, rotator cuff defect at 12 months).

## Methods and analysis

### Study design and setting

This is a prospective multicentre cohort study of patients undergoing ARCR with 17 participating orthopaedic centres in Switzerland and 1 German centre.

Several subprojects, associated with the main ARCR cohort study, are planned and include a systematic review of prognostic studies in ARCR, the application of the ARCR CES 1.0 for AE documentation, and the application and validation of an AE severity classification.

### Eligibility criteria

Adult patients diagnosed with a partial or full-thickness rotator cuff tear by MRI, planned for a primary arthroscopic surgical repair and giving their informed consent to participate in the cohort study will be included. Patients undergoing a specific surgical procedure for irreparable tears (ie, tendon transfer, subacromial spacer or superior capsular reconstruction), revision operations, and open or mini-open reconstructions will be excluded. Patients unable to provide written informed consent or attend clinics for follow-up visits, not fluent in German, French, Italian or English, or pregnant women will be excluded.

Patients undergoing bilateral ARCR will only be included for their first intervention.

### Intervention

Shoulder arthroscopies will be performed according to standardised clinic-specific and international guidelines^37^ in the context of routine care, with patients in a beach-chair or lateral decubitus position under general or local anaesthesia. The variability in the repair techniques used between clinics and surgeons will be documented. Typically, after the diagnostic arthroscopy to assess the type of rotator cuff tear (partial or full-thickness tear and involved tendons, tendon tear delamination, sign of tendon degeneration) and concomitant injuries or lesions, the ruptured tendons are mobilised until they can be repositioned on the original footprint with as little tension as possible. Tendon fixation may be performed using one of multiple anchor and suture configurations according to the surgeon’s decision. An intervention at the biceps tendon is performed if any tendinopathy or lesions to the superior labrum or biceps pulley system are observed. An anterolateral or lateral acromioplasty is performed at the surgeon’s discretion, generally in the presence of a hook-shaped acromion or a critical shoulder angle larger than 35°, respectively. Operative details, including additional concomitant procedures (acromioplasty, acromioclavicular joint resection, capsulotomy, and biceps tenotomy or tenodesis) and duration of operation, are recorded immediately after surgery. A standard three-phase postoperative rehabilitation scheme is usually prescribed and will be documented in detail, including immobilisation and passive mobilisation in the first phase, active mobilisation and coordination training in the second phase, followed by the third phase of specific progressive resistance exercises.

### Outcomes

The *first primary outcome* is the patient-reported change in shoulder functional outcome between baseline and 6 months postoperatively as measured with the OSS.^38^ The OSS is a condition-specific questionnaire developed for patients with a degenerative or inflammatory state of the shoulder. It contains 12 items to be answered by the patient independently, which deal with pain (degree, time point) and possible handicaps in private and professional life. There are five categories of response to every question, corresponding to a score ranging from 0 to 4. Scores are summed to give a single score ranging from 0 (worst outcome) to 48 (best outcome). Transcultural validations of this questionnaire for the German and Italian populations have been performed^39 40^ and are validated for patient-based outcomes after rotator cuff repair.^41–43^ While functional outcome at the last 24-month follow-up is clinically relevant, the early 6-month primary time point is chosen because of the importance in early surgical recovery and rehabilitation, particularly when considering the socioeconomic impact on professionally active patients.^4^

The *second primary outcome* is the occurrence of shoulder stiffness within 6 months after surgery: this event is poorly defined in the literature.^19^ We formed a consensus definition of shoulder stiffness among specialised shoulder surgeons in a Delphi survey, which describes a postoperative restriction in passive shoulder motion diagnosed within 6 months after ARCR in at least two of the motion planes of flexion, abduction and external rotation in 0° abduction. Motion restriction is to be assessed separately for each plane according to specific threshold criteria (flexion: total motion equal to or below 90° or glenohumeral motion equal to or below 80°; abduction: total motion equal to or below 80° or glenohumeral motion equal to or below 60°; external rotation in 0° abduction: glenohumeral motion equal to or below 20° or no more than 50% of the contralateral side value). In this project, we will identify cases of shoulder stiffness based on our consensus definition as well as clinical records and reports from clinicians and their patients.

The secondary outcomes will include (1) local AEs according to the ARCR CES, in particular the occurrence of recurrent defect of repaired tendon(s) at 12 months, when at least one repaired tendon is diagnosed with a recurrent defect by ultrasound examination, persistent or worsening pain, infection, and any local event (composite outcome); (2) functional parameters of the Constant Score (CS)^44^ at 6 and 12 months, shoulder strength (kg) in abduction at 6 and 12 months, patient-reported shoulder pain on the Numeric Rating Scale (NRS) at 6, 12 and 24 months, and patient-reported shoulder function: OSS at 6, 12 and 24 months, subjective shoulder value^45^ assessment at 6, 12 and 24 months; (3) general health and socioeconomic parameters including patient-reported quality of sleep (NRS) at 6, 12 and 24 months,^46^ return to work, change of working condition within 6, 12 and 24 months, level of depression and anxiety at 6, 12 and 24 months based on Patient-Reported Outcomes Measurement Information System (PROMIS) scores,^47 48^ patient-perceived shoulder improvement, acceptability of own symptom state,^49^ quality of life (utilities and general health) at 6, 12 and 24 months using the European Quality of Life 5 Dimensions 5 Level questionnaire (EQ-5D-5L), and patient satisfaction with the surgical outcome at 12 and 24 months; and (4) safety outcome assessment, occurrence of all AEs reported by clinicians and patients (including non-local AEs within 6 months after surgery), final independent surgeon and patient-rated assessment of AEs according to perceived severity (rating scale from 0 (no complication) to 100 (death)^50^), and Comprehensive Complication Index^50^ considering all AEs that occurred within 6 months after surgery.

Shoulder ultrasound examinations will be performed at 12 months by experienced clinicians independent of the operating surgeons. The repair integrity will be graded according to an adaptation of the Sugaya classification (where, when using MRI images, grade 4 or 5 defines the occurrence of a recurrent effect).^51 52^ Other ultrasound parameters include the location of the recurrent defect (at the footprint/medial cuff failure), long biceps tendon status, signs of anchor displacement, and location and signs of suture cut-through.

### Participant timeline

Local investigators will identify patients who meet the eligibility criteria. Patient enrolment started on 1 June 2020 and is planned for a maximum period of 15 months. Patients will complete a preoperative evaluation no more than 2 months before surgery. Follow-up assessments will be performed at 6 weeks (±1 week) and at 6 (±1 month), 12 (±1 month) and 24 (±2 months) months postoperatively. At the final 24-month time point, only patient self-reporting assessments, including surveys on AEs, will be documented (figure 1). The end date for the study representing the collection of the last patient questionnaire is expected on 1 November 2023.

**Figure 1 F1:**
[figure not shown]
Flow chart of study procedures. AE survey: surgeon and patient survey regarding AE severity (sev). Motion: shoulder range of motion. Rehab: recall on postoperative rehabilitation. *If MRI not possible. AE, adverse event; CES, core event set; CS, Constant Score; CT, arthro-CT; DE, German; EN, English; EQ-5D-5L, European Quality of Life 5 Dimensions 5 Level questionnaire; FR, French; FU, follow-up; IT, Italian; NRS, Numeric Rating Scale; OSS, Oxford Shoulder Score; RC, rotator cuff; SSV, subjective shoulder value.

### Baseline prognostic factors

Various baseline parameters, operative details and postoperative management variables are known or suspected to influence ARCR outcomes.^31–35^

The following patient-related factors will be recorded: patient demographics (year of birth, age, sex), socioeconomic parameters (nationality, marital status, highest level of education, employment status, last occupational position, daily physical workload), dominant side, smoking and drinking status, general physical and mental health (body mass index and obesity), American Society of Anesthesiologists classification, comorbidities (eg, diabetes), concomitant medication, level of depression and anxiety (PROMIS Depression and Anxiety Short Form 4a),^47 48^ and quality of life (EQ-5D-5L).^53^

Disease-related factors are shoulder clinical examinations (pain level on NRS, range of motion, muscle strength, CS^44^), patient-reported shoulder function (see Outcomes section), radiograph parameters (critical shoulder angle,^54^ acromiohumeral distance^55^), MRI or arthro-CT parameters (supraspinatus muscle atrophy,^56^ tangent sign,^57^ grade of fatty infiltration^58 59^) and medical history (cause of injury (trauma event), symptom duration, previous interventions (operation and timing of surgery), actual medication, extent of physical therapy).

Rotator cuff integrity and concomitant local findings will be investigated. The rotator cuff tear will be determined by MRI (or arthro-CT) and confirmed intraoperatively: tear size, location (involved tendons) and grading (partial/complete), tendon retraction grade^60^ and tear sagittal size,^61^ status of the biceps tendon, and additional intraoperative observation of concomitant local injuries (superior labrum from anterior to posterior (SLAP) lesion, humeral avulsion glenohumeral ligament, Bankart lesion, humeral and glenoid-side chondral lesions).

Operative details and postoperative management will also be investigated: type of ARCR procedure (use of anchors, suture techniques), augmentation techniques (eg, platelet concentrates, scaffolds and so on),^62^ additional concomitant treatment (acromioplasty, acromioclavicular joint resection, capsulotomy, biceps tenotomy or tenodesis, treatment of SLAP lesion), duration of operation, duration of hospital stay, and postoperative management (immobilisation position and duration, pain medication (eg, using non-steroidal anti-inflammatory drugs), timing of passive and active shoulder motion, and physiotherapy and muscle training).

### AE documentation and assessment process

The operating surgeons will report the occurrence of any intraoperative AE on the operation form. The occurrence of postoperative local AEs within 24 months will be reported by investigators at the clinical examination and by patients on the questionnaires. The occurrence of postoperative non-local AEs that are unrelated to the operation will be documented in a similar manner, however only within 6 months after surgery. An AE form was developed according to the ARCR CES 1.0.^23^ Each AE documentation will be structured after Audigé *et al*^63^ and includes the date/period of occurrence (intraoperative/postoperative), the affected body location (local at the operated shoulder/non-local), the event group and specification, applied health-related intervention(s) (operative/non-operative procedure(s)), its outcome at the time of reporting (or end of the study), and the assessment of the event (causal factor(s)/severity grade/seriousness). Severity grading will be made according to existing and adapted systems for intraoperative^64 65^ and postoperative^12 36^ complications.

The documentation of AEs will be checked for completeness and consistency remotely as well as on-site by reviewing selected patient files as part of the monitoring plan. A review committee ([name]) will assess all events reported by surgeons and patients and generate queries to the respective sites as required.

Fully documented local events, including their treatment, outcome and possible causative factors, will be formulated in layman’s terms and sent back to the affected patients so that they can confirm and validate collected AE data as well as assess their severity on a Visual Analogue Scale from 0 (not at all severe) to 100 (extremely severe). This subsequent rating will also be performed by their treating surgeon and four other randomly selected surgeons involved in the project, blinded to the original severity grading.

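### The AE collection rule limits postoperative non-local events to those unrelated to surgery, which contradicts safety outcomes that count all AEs within 6 months

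*Protocol article*

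**What the plan says.** The section on AE documentation and assessment process sets out three streams of collection.

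- Intraoperative: "The operating surgeons will report the occurrence of any intraoperative AE on the operation form".
- Postoperative, local: "The occurrence of postoperative local AEs within 24 months will be reported by investigators at the clinical examination and by patients on the questionnaires".
- Postoperative, non-local: "postoperative non-local AEs that are unrelated to the operation will be documented in a similar manner, however only within 6 months after surgery".

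The same section describes the AE form. It records "the affected body location (local at the operated shoulder/non-local") and "the assessment of the event (causal factor(s)/severity grade/seriousness") for each event. A review committee "will assess all events reported by surgeons and patients" and can query the sites.

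In the Outcomes section, the safety block of the secondary outcomes includes the "occurrence of all AEs reported by clinicians and patients (including non-local AEs within 6 months after surgery"), and the Comprehensive Complication Index "considering all AEs that occurred within 6 months after surgery". Neither definition is restricted by relation to the operation.

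**The concern.** The third stream carries a qualifier that the other two lack: it admits a non-local event only if the operation did not cause it. Taken at its word, a site would record a systemic event that has nothing to do with surgery and would have no instruction to record one that surgery brought about. The second kind matters more to a safety assessment, and the outcome definitions plainly include it.

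What is at stake is part of the secondary safety block: the occurrence of all AEs to 6 months and the Comprehensive Complication Index. An outcome definition cannot bring back an event that was never entered. With 17 Swiss centres and 1 German centre, sites may also read the sentence differently, and differences in recording could then pass for differences between clinics.

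**Working it through.** No figure in the plan bears on this point, so the check compares texts. Events are classified by period, location and relation to the operation. Each class is then set against the collection rule and against what the Outcomes section requires within 6 months.

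| Class of AE | Collection rule | Needed for the all-AE outcome and the index to 6 months |
|---|---|---|
| Intraoperative, any location, any cause | Covered | Yes |
| Postoperative, local, related | Covered to 24 months | Yes |
| Postoperative, local, unrelated | Covered to 24 months | Yes |
| Postoperative, non-local, unrelated | Covered to 6 months | Yes |
| Postoperative, non-local, related | No rule stated | Yes |

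One class is required but not covered.

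**Can another reading of the sentence close the gap?**

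1. The qualifier is a loose description of non-local events in general. The sentence would then treat every non-local event as unrelated to surgery, although the form asks for causal factors for each AE whatever its location. The intent would be harmless, but the wording would still be wrong.
2. Only unrelated non-local events stop at 6 months, and related ones run to 24 months. The 24-month rule is stated for local events only, and the Outcomes section applies 6 months to non-local AEs without distinction.
3. The qualifier is a true filter. It then contradicts the Outcomes section directly.

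The sentence needs correcting on each reading.

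**Would the other checks recover an omitted event?** The committee works on events that have been reported. On-site review looks at selected patient files. Confirmation by patients is described for fully documented local events. Each may find some omissions, but none is aimed at this class.

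**Direction of the error if the rule is followed literally.** An unrecorded event can take a patient out of the numerator of the all-AE proportion (if that patient has no other recorded event) while the patient stays in the denominator. It can lower that patient's index or leave it unchanged. Neither quantity can rise, so any error runs towards looking safer.

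**The case against.** The strongest reply is that nothing has been shown to be lost. The text is a journal article that condenses a full protocol, and sites work from forms and questionnaires that are not shown. The form as described has a non-local category and a causal-factor item, and nothing says that it screens out related events. The qualifier sits in a sentence whose main purpose is to contrast 24 months for local events with 6 months for non-local ones, so it may be careless phrasing. Patients report events too, monitoring looks at files, and the committee can raise queries. The Adverse events section also provides for analysing events outside the core event set and its periods, so the listed categories are not a closed gate.

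Most of this stands as a limit on the claim. A reader might infer that operation-related systemic complications drop out of the safety outcomes and the index. The document does not support that: the Outcomes section includes them expressly, and a site working to that section would capture them. A reader might also suppose that all general complications of surgery or anaesthesia are missed, but those occurring during the operation are reported under the first stream.

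The reply does not rescue the wording. The sentence is grammatically restrictive, it is the article's only statement of which non-local events are documented, and it disagrees with the outcomes it is meant to feed.

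**Conclusion.** The contradiction is real and should be corrected. As worded, the collection rule covers fewer events than the safety outcome and the Comprehensive Complication Index require, and the uncovered class is postoperative, non-local and related to the operation. If a site applies the rule literally, these outcomes will be understated at that site.

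The size cannot be derived: the document gives neither a rate for such events nor any sign of how sites read the rule. A reader might try to count missing patients. An assumed rate of 0.5% to 2% among 970 patients gives 0.005 × 970 = 4.9 to 0.02 × 970 = 19.4, or about 5 to 19. That rests on a rate with no source in the document and on every such event being missed at every site, so it illustrates scale and is not an estimate.

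The change in OSS and the occurrence of stiffness, the two primary outcomes, are unaffected. So are the incidence of local AEs and the validation of the local severity classification. The point matters because quantifying AE incidence is a stated secondary objective, but it concerns one part of the secondary safety outcomes.

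**What to change.** Reconcile the two sections by deleting, in AE documentation and assessment process, the clause that limits non-local events to those unrelated to the operation. All postoperative non-local AEs within 6 months are then documented, in line with the Outcomes section, and relatedness is recorded in the causal-factor item for each event. If the full protocol or the site instructions carry the same clause, change it there too.

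Send sites a short clarification. Have the review committee ask whether any site applied the restrictive reading, and query patients already enrolled only at sites that did. Enrolment began on 1 June 2020, so this check is easier the sooner it is made.

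The cost is one wording change, one note to sites, one question from the committee and, at most, a limited set of retrospective queries. The AE form needs no new field, and neither the sample size nor the primary analyses change.
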